#### **4.1.2 Exclusion Criteria**

Patients meeting any of the following criteria will be excluded from the study:

1. Diagnosis of a significant CNS disease other than FTD that may be a cause for the patient's FTD symptoms or may confound study objectives.

2. Brain MRI/magnetic resonance angiography (MRA) imaging indicating clinically significant abnormality, including evidence of prior hemorrhage, infarct  $>1 \text{ cm}^3$  or  $>3$  lacunar infarcts, or a structural or vascular abnormality deemed a contraindication to intracisternal injection.
3. Hypersensitivity or contraindications to corticosteroid and/or sirolimus use (including but not limited to osteoporosis with vertebral fractures within 1 year prior to Screening, poorly controlled diabetes [see Exclusion Criterion 5c], uncontrolled hypertension [see Exclusion Criterion 5f]), uncontrolled hyperlipidemia or hypercholesterolemia as per Investigator assessment, uncontrolled interstitial lung disease, or uncontrolled renal insufficiency).
4. Clinical evidence of peripheral symmetric sensory polyneuropathy (stable sensory mononeuropathies and radiculopathies are not exclusionary).
5. Concomitant disease or condition within 6 months of Screening that could interfere with, or treatment of which might interfere with, the conduct of the study or that would, in the opinion of the Investigator, pose an unacceptable safety risk to the patient or interfere with the patient's ability to comply with study procedures; including, but not limited to, the following:
  - a. Evidence of clinically significant liver disease
  - b. Unstable autoimmune disease requiring chronic immunosuppression
  - c. Poorly controlled/not adequately managed diabetes (Screening hemoglobin A1c [HbA1c]  $\geq 7\%$ )
  - d. History of unstable angina, myocardial infarction, chronic heart failure (New York Heart Association Class III or IV), or clinically significant conduction abnormalities (e.g., unstable atrial fibrillation) within 1 year prior to Screening
  - e. Clinically significant 12-lead ECG abnormalities at Screening, as determined by the Investigator

- f. Uncontrolled hypertension defined as: average of 3 systolic blood pressure [SBP]/diastolic blood pressure [DBP] readings >165/100 mm Hg at Screening, or persistent SBP/DBP readings >180/100 mm Hg within 3 months prior to Screening that, in the opinion of the Investigator, are indicative of chronic uncontrolled hypertension
- g. History of cancer within 5 years of Screening or current presence of pre-cancer lesions, with the exception of fully excised nonmelanoma skin cancers and fully excised prostate carcinoma in situ that have been stable for at least 6 months
- h. History or current alcohol or drug abuse within 2 years of Screening
- i. Any current psychiatric diagnosis according to the Diagnostic and Statistical Manual of Mental Disorders Fifth Edition, International Statistical Classification of Diseases and Related Health Problems Tenth Revision, or equivalent, that may interfere with the patient's ability to perform study procedures and all assessments (e.g., psychosis, major depression, bipolar disorder, mental retardation, and schizophrenia).  
NOTE: Psychiatric manifestations of FTD are not exclusionary
- j. At imminent risk of self-harm, based on clinical interview and responses on the C-SSRS. Patient must be excluded if they report ideation with intent, with or without a plan or method (i.e., positive response to item 4 or 5 on the C-SSRS) in the past 2 months or suicidal behavior in the past 6 months
- k. Any medical disorders that, in the opinion of the Investigator, could interfere with study-related procedures (including safe performance of lumbar puncture (LP) or intracisternal injection), such as prohibitive spinal diseases, bleeding diathesis, clinically significant coagulopathy, thrombocytopenia, or increased intracranial pressure
- l. Documented stroke or transient ischemic attack within 1 year prior to Screening
- m. History of seizure or unexplained blackouts, with the exception of seizure due to known, transient cause (e.g., medication, electrolyte disturbance), within 10 years prior to Screening

- n. Currently active infection or severe infection (e.g., pneumonia, septicemia, CNS infections [e.g., meningitis, encephalitis]) within 12 weeks prior to Screening
  - o. History of severe allergic or anaphylactic reactions. History of hypersensitivity to any inactive ingredient of the investigational product (refer to the IB) or protocol-required immunosuppressant medications
  - p. Clinical evidence of vitamin B12 deficiency or vitamin B12 level less than the lower limit of normal if deemed clinically significant as per Investigator's assessment at Screening
  - q. History of neurosyphilis or history of syphilis infection without documentation of adequate treatment.
  - r. Subject is generally frail or has any medical condition, for which in the view of the investigator, participation in the study would not be in the best interest of the subject or is likely to prohibit further participation during the study period
6. Clinically significant abnormalities in laboratory test results at Screening as given below (laboratory testing may be repeated with medical monitor approval):
- a. Total bilirubin, alanine aminotransferase, or aspartate aminotransferase  $>1.5 \times$  the upper limit of normal (ULN) (note: patients with confirmed Gilbert syndrome are allowed for enrollment with Sponsor's agreement)
  - b. Serum creatinine  $>1.5 \times$  ULN
  - c. Hematocrit  $<35\%$  for men and  $<32\%$  for women
  - d. Absolute neutrophil count  $<1500/\mu\text{L}$
  - e. Platelet count  $<100\,000/\mu\text{L}$
  - f. International normalized ratio  $>1.4$  or other coagulopathy.
  - g. Activated partial thromboplastin time  $>50$  seconds
  - h. Thyrotropin (TSH) level outside the normal range and deemed clinically significant by the Investigator

- i. Positive result for hepatitis B surface antigen, hepatitis C antibody, or human immunodeficiency virus (HIV) 1 or 2.
  - j. Any other abnormal Screening laboratory test result deemed clinically significant by the Investigator.
- 7. Participation within 3 months prior to Screening in another therapeutic investigational drug or device study with purported disease-modifying effects on FTD, unless it can be documented that the patient received placebo only.
- 8. Any type of prior gene or cell therapy.
- 9. Immunizations (live vaccines) in the 4 weeks prior to Screening. Note: Pneumococcal vaccine and shingles vaccine administration is allowed during the Screening Period (patients not previously vaccinated should receive pneumococcal and/or shingles vaccine administration at least 4 weeks prior to sirolimus loading dose).
- 10. Use of blood thinners (e.g., warfarin, heparin, and novel oral anticoagulants) in the 2 weeks prior to Screening or the anticipated need to initiate blood thinners during the study. Antiplatelet therapies (prophylactic aspirin, clopidogrel) are acceptable if the patient is medically able to temporarily stop from at least 7 days prior to and at least 48 hours after intracisternal injection and LP.
- 11. Contraindications or intolerance to imaging methods (MRI, CT) inducing claustrophobia and intolerance to contrast agents used for MRI or CT (including but not limited to gadolinium contrast agents and iohexol).
- 12. Contraindications to general anesthesia or deep sedation.
- 13. Positive urine test for drugs of abuse (including opiates, amphetamines, cocaine, barbiturates, and phencyclidine) without prescription at Screening and Day -1. Note: Use of medical marijuana is permitted provided that the patient is on a stable regimen. It is also permitted if the patient resides in a state in which the recreational use of marijuana is legalized, so long as the patient does not meet drug abuse criteria (as defined in the Diagnostic and Statistical Manual of Mental Disorders, Fifth Edition).

## **4.2 Withdrawal of Patients from Study Treatment and/or the Study**

The duration of the study is defined for each patient as the date signed written informed consent is provided through the last follow-up visit.

### **4.2.1 Reasons for Withdrawal/Discontinuation**

Patients may withdraw from the study at any time and for any reason without prejudice to their future medical care by the Investigator or at the study site that is provided outside of this study. An excessive rate of withdrawals can affect the integrity of the study, and unnecessary withdrawal of patients should be avoided. The Investigator also has the right to withdraw a patient from the study in case of events as provided below or for other reasons. The reasons for patients not completing the study will be recorded in the electronic case report form (eCRF). Prior to discontinuing any patients, the Investigator should discuss the reasons with the Sponsor or delegate.

A patient may be withdrawn from the study for any of the following reasons:

1. The patient withdraws consent or requests discontinuation from the study for any reason.
2. Occurrence of any medical condition or circumstance that exposes the patient to substantial risk and/or does not allow the patient to adhere to the requirements of the protocol.
3. Any SAE, clinically significant AE, severe laboratory abnormality, intercurrent illness, or other medical condition that indicates to the Investigator that continued participation is not in the best interest of the patient.
4. Patient failure to comply with protocol requirements or study-related procedures.
5. Termination of the study by the Sponsor or the regulatory authority.

Upon occurrence of a serious or intolerable AE, the Investigator will confer with the Sponsor. If a patient is discontinued because of an AE, the event will be followed, to the greatest extent possible, until it is resolved or stabilized.

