### **4.2.4 Study Stopping Rules**

Each patient will receive only 1 dose of PR006A once during the course of the study; hence, stopping rules apply only during the Screening Period. Patients who have been dosed with PR006A will be followed to the end of the study as per protocol.

If any one of the following criteria are met, PR006A dosing will be paused and further enrollment across all study sites will be halted until the iDMC evaluates all available study data and makes a recommendation:

- More than  $5 \times$  ULN increase in ALT, AST, or both in any patient after PR006A administration that is not manageable by corticosteroid treatment implemented according to AASLD guidelines ([Manns et al 2010](#)).
- The occurrence of 2 or more of any 1 of the following treatment-emergent AEs (TEAEs)/SAEs (not 2 single occurrences of different AE/SAE):
  - Subarachnoid hemorrhage, cerebral macrohemorrhage
  - Grade 3 and/or 4 allergic reactions, hypersensitivity reactions, cytokine release reactions
  - Persistent neurological symptoms at least possibly attributable to the ICM investigational product administration procedure
  - CNS infections (e.g., meningitis, encephalitis)
  - Seizures, stroke, or acute paralysis
- More than 1 patient experiences any Grade 3 or higher AE that is judged as definitely, probably, or possibly attributed to PR006A.
- More than 1 Grade 3 or higher SAE that may or may not be potentially related to PR006A and that poses either an immediate risk to the patient's health or is likely to adversely affect the patient's long-term health.
- Death of a patient, after having received PR006A, that is judged as definitely, probably, or possibly attributed to PR006A. The study will be temporarily stopped in order to undergo review by the institutional review board (IRB)/independent ethics committee (IEC), iDMC, and other health authorities.
- The occurrence of a malignancy at any point after gene transfer that is judged per the Sponsor's final causality assessment as related to PR006A.

The study may be terminated if one or more of the following criteria are met:

1. The Sponsor decides to terminate the study based upon an assessment of safety.
2. The Sponsor decides to terminate the study for administrative reasons.

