discontinuation. The iDMC will assess safety variables as listed for the primary safety endpoints ([Section 2](#)) and as detailed in [Section 11.1.1](#). Patients must have evidence of a negative MTB test and pneumococcal pneumonia and shingles vaccination coverage (within 10 years prior to Screening; allowed during Screening Period but at least 4 weeks prior to sirolimus loading dose) in order to initiate prednisone or sirolimus. Additionally, if medically indicated and as per local standard of care, Principal Investigators may consider performing EBV, CMV, and JC virus testing as well anti-viral (e.g., valganciclovir) and/or antibacterial (e.g., low-dose Bactrim) prophylaxis during sirolimus course.

If steroid or sirolimus side effects emerge, these drugs will be stopped or tapered as medically indicated. Details regarding additional monitoring for corticosteroid and sirolimus-related events are provided in [Section 5.5.1.3](#)

If clinically indicated and/or as per local practice, concomitant gastroprotective prophylactic medication, as well as potassium and/or calcium/vitamin D3 and bisphosphonate supplementation, may be initiated. Specifically, for patients with pre-existing osteoporosis (without history of vertebral fracture in the past year) or history of fragility fracture, the Investigator should consider prescribing appropriate therapy intended to prevent/attenuate glucocorticoid-induced osteoporosis starting at the time of initiation of prednisone administration. The same consideration to provide therapy to prevent/attenuate glucocorticoid induced osteoporosis should be given to patients whose prednisone treatment may be extended beyond 6 weeks. A dual-energy x-ray absorptiometry (DEXA) scan will be performed at Screening and will be repeated at Month 12 for patients with baseline osteopenia or osteoporosis ([Section 6.16](#)). For patients receiving prednisone for more than 3 months, HbA1c will be measured at the end of prednisone therapy.

Continued participation in the study will not be affected if the patient or Investigator finds corticosteroid administration to be intolerable or the patient develops clinically significant AEs requiring early prednisone or sirolimus discontinuation.

The following TEAEs, which may be associated with immunosuppressant regimen (see above text), should be explicitly monitored:

- Peptic ulcer disease
- Erosive gastritis

- Osteoporosis
- Increase in body weight  $\geq 5\%$  from baseline

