### **7.1 Primary Endpoints**

#### **7.1.1 Primary Safety Endpoints**

The following primary safety endpoints are measured up to 5 years:

- Incidence and severity of TEAEs and SAEs, including clinically significant changes in vital signs, clinical laboratory assessments, C-SSRS, and TNAS; treatment-emergent transaminitis; treatment-emergent diabetes and prediabetes; treatment-emergent peptic ulcer disease and/or erosive gastritis; treatment-emergent osteoporosis; treatment-emergent increase in body weight  $\geq 5\%$  from baseline, treatment-emergent BMI  $>25$  or  $>30$ , and treatment-emergent increase in waist circumference  $\geq 15\%$  from baseline; incidence of Grade  $\geq 3$  infections; incidence/aggravation of psychosis; treatment-emergent hypercholesterolemia or hyperlipidemia; treatment-emergent interstitial lung disease; treatment-emergent opportunistic infections (including progressive multifocal leukoencephalopathy (PML) and BK virus-associated nephropathy); sirolimus trough levels; 12-lead ECGs; brain MRIs; physical examinations; and neurological examinations
- Sum of ARs and suspected ARs
- Sum of serious ARs and serious suspected ARs
- Incidence of procedure or treatment-emergent safety findings as per brain MRI.
- Change from baseline in immunogenicity of AAV9 and PGRN in blood at Day 14 and Months 1, 2, 3, 6, 9, and 12 and in CSF at Months 2 and 12.

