### **11.2.2 Protocol Deviations**

A deviation from the protocol is an unintended or unanticipated departure from the procedures or processes approved by the Sponsor and the IRB/IEC and agreed to by the Investigator. A significant deviation occurs when there is nonadherence to the protocol by the patient or Investigator that results in a significant, additional risk to the patient. Significant deviations can include nonadherence to inclusion or exclusion criteria, or nonadherence to FDA regulations or ICH GCP guidelines, and may lead to the patient being withdrawn from the study ([Section 4.2](#)). Further terms concerning protocol deviations including reporting of protocol deviations will be set forth in the CTA entered into by the Sponsor, the Investigator, and the institution.

In the unlikely event that there is a deviation from the protocol, the Investigator or designee must document and explain in the patient's source documentation such deviation from the approved protocol. The Sponsor and IRB/IEC must be notified. The Investigator may implement a deviation from, or a change of, the protocol only to eliminate an immediate hazard to study patients without prior Sponsor or IRB/IEC approval. As soon as possible after such an occurrence, the implemented deviation or change, the reasons for it, and any proposed protocol amendments should be submitted to the IRB/IEC for review and approval, to the Sponsor for agreement, and to the regulatory authorities, if required.

Protocol deviations will be documented by the clinical monitor in the monitoring visit report throughout the course of monitoring visits. Investigators will be notified in writing by the

monitor of deviations. The IRB/IEC should be notified of all protocol deviations in a timely manner.

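### Study withdrawal for harm, non-compliance or deviation is not limited to undosed patients, conflicts with Section 4.2.4, and may cost dosed patients part of their 5-year safety follow-up

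*Protocol*

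**What the plan says.** All references are to the protocol.

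- **Section 4.2.1** opens its list with "A patient may be withdrawn from the study for any of the following reasons". What ends is study participation, not only treatment. Item 3 reads "Any SAE, clinically significant AE, severe laboratory abnormality, intercurrent illness, or other medical condition" and goes on to require that, in the Investigator's judgement, staying in is not in the patient's best interest. Item 4 is "Patient failure to comply with protocol requirements or study-related procedures". Item 2 covers conditions that expose the patient to substantial risk or prevent adherence. The section also says that needless withdrawals should be avoided, that the Investigator should first discuss the reasons with the Sponsor, and that an AE leading to discontinuation is followed until it resolves or stabilises.
- **Section 4.2.2** lets the Investigator or the Sponsor end participation at any time. For dosed patients it urges at least AE assessments, by phone if necessary. It asks sites to try to obtain a termination panel and, after an early exit, a return at the scheduled Month 12 (Year 1 withdrawals) or Month 60 (later withdrawals).
- **Section 11.2.2** says that significant deviations, including eligibility breaches, "may lead to the patient being withdrawn from the study".
- **Section 4.2.4** states: "Patients who have been dosed with PR006A will be followed to the end of the study as per protocol".
- **Section 6.2.1.3** has AEs assessed up to the patient's exit from the study. **Section 4.2.3** rules out replacement.
- **Section 7.1.1** states: "The following primary safety endpoints are measured up to 5 years".

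**The concern.** With a single administration, taking a dosed patient out of the study does not undo the PR006A exposure, but it can end the observation on which the primary safety objective depends. The grounds in items 2 to 4, in Section 4.2.2 and in Section 11.2.2 can apply to a patient who has not withdrawn consent. Several of them are triggered by harm or are close to it. Follow-up lost this way is related to outcome: the patients most informative about late toxicity are the likeliest to leave.

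A site also cannot tell which rule governs. Section 4.2.4 promises follow-up of dosed patients to the end of the study, while Section 4.2.1 allows the same patients to be taken out. In a first-in-human study with 5 patients per cohort and no replacement, one such exit is a fifth of what is known about a dose in the long term. The malignancy stopping criterion, which applies at any time after gene transfer, also relies on dosed patients still being observed.

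**Working it through.** **Inputs.** One dose per patient (Section 4.2.4). Fifteen patients in 3 cohorts of 5, with no power basis (Section 7.4). Primary safety up to 5 years (Section 7.1.1). Termination and return rules (Section 4.2.2). Follow-up visits at Months 18, 24, 30, 36, 42, 48, 54 and 60 (Table 13-2).

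**1. The plan's own figure.** 3 × 5 = 15, which agrees. There is no power calculation to reproduce.

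**2. The passages side by side.**

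| Question | 4.2.1, 4.2.2, 11.2.2 | 4.2.4 |
|---|---|---|
| May a dosed, consenting patient be taken out of the study? | Yes, at discretion, on the listed grounds | No exception named |
| Are dosed and undosed patients separated? | Not in the withdrawal grounds; only in the follow-up requests of 4.2.2 | Yes |
| What follows withdrawal? | AE contact, a termination panel and one return visit, all best effort | Follow-up to end of study |

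**3. Follow-up without a named visit after a Year 1 withdrawal**, giving full credit for the Month 12 return:

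- Months: 60 − 12 = 48, and 48/60 = 80% of that patient's follow-up. All 8 follow-up visits fall in this gap.
- Cohort: 5 patients × 5 years = 25 person-years planned. 48 months = 4 years, and 4/25 = 16% per patient lost.

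**4. What one lost patient does to a cohort.** The protocol gives no late-event rate, so 10% and 20% are assumed. The chance of seeing at least one event is 1 − (1 − p)^n. The one-sided 95% upper bound after zero events is 1 − 0.05^(1/n).

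| Patients followed | Chance, p = 10% | Chance, p = 20% | Upper bound after 0 events |
|---|---|---|---|
| 5 | 41.0% | 67.2% | 45.1% |
| 4 | 34.4% | 59.0% | 52.7% |
| 3 | 27.1% | 48.8% | 63.2% |

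**5. Outcome-related loss.** Suppose 1 of 5 patients is harmed early and has a late-event risk of 30% to 50%, while the other 4 have 10% (all assumed). The expected cohort rate is (0.30 + 4 × 0.10)/5 = 14% to (0.50 + 4 × 0.10)/5 = 18%. If only the other 4 are observed, it is 10%. If early harm carries no extra late risk, loss of that patient costs precision but does not shift the rate.

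**The case against.** The strongest reply is that the protocol saw this problem. Section 4.2.2 gives the single administration of gene therapy as its reason for urging AE assessment of every dosed patient, by phone if need be, and it asks for a termination panel and a later return visit. Table 13-2 allows remote follow-up visits. Section 6.2.1.6 asks for related SAEs even after 5 years. Item 3 is conditional on best interest. The sentence in Section 4.2.4 stands among the stopping rules and is qualified by reference to the protocol, so it could be read as subject to Section 4.2.1.

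Much of this stands, and it rules out several stronger readings:

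- **That harmed patients lose their 5-year follow-up, or that new later events go uncovered.** The AE contacts and return visits are not limited to the event that led to withdrawal.
- **That a Month 6 withdrawal loses 54 of 60 months (90%, or 4.5/25 = 18% of the cohort's follow-up).** This is the worst case, in which every safeguard fails.
- **That withdrawal removes no exposure.** This is true of PR006A only. Sirolimus continues for about 3 months plus a taper, and lumbar punctures are scheduled at Months 2 and 12.
- **That withdrawn patients are counted as event-free.** No section says so. Section 7.5 only defines the analysis set, and Section 7.7 leaves conventions to the SAP.
- **That Section 6.2.2.2 contradicts Section 4.2.1.** Its rule, "Continued participation in the study will not be affected if the patient or Investigator finds corticosteroid administration to be intolerable", is specific to the immunosuppressants and can coexist with a general right of withdrawal. It shows that the protocol can keep an intolerable drug apart from leaving the study.

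What the reply does not remove is that the safeguards are encouragement and best effort, and that for a Year 1 withdrawal they name no visit after Month 12. If Section 4.2.4 is read as subject to Section 4.2.1, it assures nothing to the patients concerned.

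**Conclusion.** The point holds in a limited form. The protocol lets dosed, consenting patients be taken out of the study on grounds linked to harm, non-compliance or deviation, against Section 4.2.4. The mitigation in Section 4.2.2 does not secure the period in which late toxicity would appear. For each Year 1 withdrawal, 80% of the patient's planned follow-up and 16% of the cohort's person-years rest on general encouragement alone.

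This assumes a full cohort of 5, that the Month 12 return takes place, and that nothing is obtained afterwards; any later phone contact reduces the loss. How often such withdrawals would occur cannot be judged from the protocol. The shift in an observed event rate depends on the assumed link between early harm and late risk, and on analysis conventions not shown here.

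The matter is moderate: the analysis is descriptive and partial safeguards exist. It is still worth correcting, because the loss would fall on the primary objective and could not be recovered later.

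**What to change.** Reconcile Sections 4.2.1, 4.2.2, 4.2.4 and 11.2.2 with one rule for dosed patients who have not withdrawn consent. An SAE, AE, laboratory abnormality, other medical condition, non-compliance or significant deviation should lead to omission of the procedures that the Investigator judges unsafe or the patient refuses. It should not lead to exit from the study. AE and SAE follow-up then continues at the planned visits to Month 60, by phone or video where needed, as Table 13-2 already permits. The present wording can remain for patients not yet dosed.

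The Investigator's best-interest judgement over procedures stays intact. Item 5 of Section 4.2.1, on termination by the Sponsor or a regulatory authority, need not be rewritten.

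The cost is wording in an amendment. No patients or visits are added, since 5-year follow-up is already planned. The small downside is that some patients will have a reduced, partly missing schedule instead of a clean exit.
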